**Objectives::**

This study aims to compare the effect of providing CR financial incentives to post-MI patients referred for outpatient CR and to confirm the effect of increasing CR participation and completion rates.

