### 2.9. Outcome evaluation

#### 2.9.1. Primary outcome.

The primary outcomes at 3 months will be the CR participation rate, defined as the number of CR sessions completed, and the CR completion rate (attendance of sessions greater than 50%; thus, completion of ≥ 18 sessions). Changes in PROM functional status using the Korean activity scale index (KASI), quality of life assessments in EuroQol 5 dimensions, and depression evaluation using the patient health questionnaire will be compared from baseline to 3, 6, and 12 months.

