#### 2.9.2. Secondary outcome.

The secondary outcomes at 3 months will be used to assess changes in cardiopulmonary endurance by 1 MET (peak oxygen consumption rate [VO_2_] 3.5 mL/kg/minutes), VO_2_ max, and VO_2_ at the anabolic threshold. At 6 and 12 months, improvement and maintenance of cardiorespiratory endurance by 1 MET (peak VO_2_ 3.5 mL/kg/minutes), VO_2_ max, and VO_2_ at anabolic threshold will be assessed.

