### 2.11. Statistical analysis

The analysis of this study was performed using an intention-to-treat and per-protocol method. CR participation, defined as the number of sessions completed, will be analyzed as a continuous variable using the student *t* test or Mann–Whitney *U* test, based on the normal distribution of the data. CR completion and categorical variables will be analyzed using chi-square or Fisher’s exact test. Missing data will be replaced using the last observation carried forward or the mean value. In the case of more than 20% of dropouts, missing data in the intent-to-treat analysis will be replaced using multiple imputations. The intention-to-treat population will include all enrolled participants, and the per-protocol analysis will include patients who have completed the 3-month evaluation.

Changes in secondary outcomes over time for the CPET, KASI, EuroQol 5 dimensions, and patient health questionnaire will be analyzed using paired t-tests with comparisons from baseline. Analyses will be conducted for each of the intervention, control, CR completion, and non-completed groups. For non-normal distributions, the Wilcoxon signed-rank test will be used.

Statistical significance will be set at *P* < .05, and SPSS version 20 (IBM SPSS Statistics, New York, NY) will be used for the statistical analysis.

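### Exercise-test and patient-reported outcomes are tested only within groups against baseline, so the plan names no randomised comparison for them

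*Protocol article*

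**What the plan says.** The protocol article, section 2.11, assigns tests by outcome.

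- Number of sessions: "will be analyzed as a continuous variable using the student *t* test or Mann–Whitney *U* test".
- Completion: "CR completion and categorical variables will be analyzed using chi-square or Fisher’s exact test".
- Exercise-test measures, KASI, EQ-5D and PHQ-9: changes over time "will be analyzed using paired t-tests with comparisons from baseline". The fallback is also a paired test: "For non-normal distributions, the Wilcoxon signed-rank test will be used".

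The paired tests are then repeated in four groups: "Analyses will be conducted for each of the intervention, control, CR completion, and non-completed groups".

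The outcome sections do not add a contrast between arms. Section 2.9.1 says the patient-reported measures "will be compared from baseline to 3, 6, and 12 months". Section 2.9.2 says: "The secondary outcomes at 3 months will be used to assess changes in cardiopulmonary endurance by 1 MET". The objective in the Abstract is to "compare the effect of providing CR financial incentives to post-MI patients referred for outpatient CR" and to confirm an effect on participation and completion.

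Section 2.9.1 also places the patient-reported measures under the primary-outcome heading, whereas section 2.11 calls them secondary.

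**The concern.** A paired test asks whether one group's mean changed from its own starting point. The question in a 1:1 randomised trial is whether the change differs between arms. After a myocardial infarction, with the same 36-session programme offered to everyone, improvement is to be expected in both arms whatever the incentive does. Two separate P values, one per arm, cannot separate that shared recovery from an incentive effect.

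The completer and non-completer tests raise a second problem. Completion means 18 or more sessions. It is observed after randomisation and is itself a primary outcome. People who attend may differ from those who do not in health, distance or motivation, so randomisation protects no contrast between the two groups.

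If section 2.11 is followed as written, the trial cannot say whether incentives change fitness, function, quality of life or depression. It also invites the reading that improvement seen only in the incentive arm, or only in completers, shows an effect.

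**Working it through.** **1. The plan's own figure.** The only sample-size figure concerns completion (section 2.5: 55.4% v 15.4%, power 0.8). Take two-sided alpha 0.05 (sidedness is not stated) and the pooled formula without continuity correction:

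n = [1.96·√(2·0.354·0.646) + 0.8416·√(0.554·0.446 + 0.154·0.846)]² / 0.40² = (1.3255 + 0.5170)² / 0.16 = 21.2, so 22 per group.

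This matches the stated 22. Allowing 10% dropout, 22/0.9 = 24.4, and the article uses 24. No figure is given for the exercise-test or patient-reported outcomes.

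**2. Which outcomes have a between-arm test.**

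| Outcome | Named test | Compares arms? |
|---|---|---|
| Number of sessions | t or Mann–Whitney U | Yes |
| Completion, categorical variables | Chi-square or Fisher | Yes |
| Exercise test, KASI, EQ-5D, PHQ-9 | Paired t or Wilcoxon signed-rank, within group | No |

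The categorical line does not fill the gap. Section 2.9.2 mentions 1 MET but defines no yes/no responder endpoint, and section 2.11 sends the exercise test to the paired tests.

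**3. How often separate tests disagree when the arms do not differ.** Assume normal change scores, the same true mean change d (in SDs of the change score) in both arms, and 24 per arm. The value of d is not in the article, so a range is shown.

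The within-arm power p comes from the non-central t distribution with 23 degrees of freedom and non-centrality d·√24. The arms are independent, so P(exactly one significant) = 2p(1 − p). For d = 0.4, p = 0.467 and 2 × 0.467 × 0.533 = 0.498.

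| d | p | Exactly one arm significant | Incentive arm only |
|---|---|---|---|
| 0 | 0.050 | 9.5% | 5% |
| 0.2 | 0.156 | 26% | 13% |
| 0.3 | 0.291 | 41% | 21% |
| 0.4 | 0.467 | 50% | 25% |
| 0.5 | 0.650 | 46% | 23% |
| 0.6 | 0.804 | 32% | 16% |
| 0.8 | 0.965 | 7% | 3.5% |
| 1.0 | 0.997 | 0.7% | 0.3% |

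The rows for 0.8 and 1.0 SD come from simulation (40,000 trials per setting). The same simulation, run at 0, 0.2, 0.4, 0.5 and 0.6 SD, agrees with the formula to within a percentage point. A two-sample t-test on the same simulated data rejected in about 5% at every setting. With 22 per arm the peak is about 49%. At 0.8 SD both arms are significant in 93% of trials.

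**4. Who the completers would be.** Read the sample-size rates as completion proportions. Expected completers are then 0.554 × 24 = 13.3 in the incentive arm and 0.154 × 24 = 3.7 in control, 17.0 in all. About 13.3/17.0 = 78% of them come from the incentive arm. A completer result would mix allocation with self-selection.

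**5. What a direct comparison can deliver.** At 24 per arm, a two-sample test of change has 80% power for a difference of 0.83 SD of the change score (0.86 SD at 22). Baseline adjustment helps. With equal variances and baseline correlation r, the ratio of change-score to ANCOVA variance is 2/(1 + r), a saving of (1 − r)/2. That is 10% at r = 0.8 and 25% at r = 0.5, where r is an assumption.

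**The case against.** The central question of the trial is attendance. The full objective, the sample size and the between-arm tests all concern participation and completion, and the affected outcomes are called secondary in section 2.11. That is true and limits the point to the exercise-test and patient-reported outcomes. It does not remove it, because section 2.9.1 places the patient-reported outcomes under the primary heading.

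The article condenses a fuller protocol, so a between-arm analysis might be specified elsewhere. But the article is not silent here: it chooses a test, gives its non-parametric substitute and lists the groups. The abstract speaks of comparing changes in these outcomes without saying between whom.

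The 26% to 50% is not the error rate of any planned test. It is how often a misleading pattern would appear, and it becomes an error only if someone reads the pattern as an arm difference. It also peaks in the middle of the assumed range and is small for large changes. Both remarks are right, which is why the full range is shown. The pattern that would flatter incentives occurs half as often, at most about 25%, against 2.5% for a direct test in that direction.

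The article makes no causal claim about completers and names no test between them and non-completers. That also stands. The remedy for that part is a label, not a deletion.

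Finally, a direct comparison in 48 people will be imprecise. That is a reason to report an interval, not to leave the comparison out.

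**Conclusion.** The concern holds. For exercise capacity, KASI, EQ-5D and PHQ-9 the only tests the article fixes are within-group tests against baseline, and none compares the randomised arms. This is a wrong choice of test stated in the text, not a detail left to an analysis plan.

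Its numerical size rests on the assumed common change. The disagreement rate exceeds the 5% of a direct test from 0 to 0.8 SD and drops below it only when both arms are almost always significant. Across that whole range the separate tests carry no valid information on the incentive effect. The attendance and completion analyses are not affected.

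**What to change.** Rewrite the second paragraph of section 2.11 along these lines:

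> For each exercise-test and patient-reported outcome, arms will be compared with a mixed model for repeated measures containing arm, visit, arm-by-visit interaction, baseline value and hospital (or ANCOVA at each visit with arm, baseline value and hospital). The adjusted difference between arms at 3, 6 and 12 months will be reported with its 95% CI. Changes from baseline within each arm will be summarised descriptively, without tests. Results by completion status are non-randomised and exploratory.

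In the same edit, give the patient-reported outcomes one status in sections 2.9.1 and 2.11. If the mixed model is chosen, state how it fits with the rules in section 2.11 for last-observation, mean and multiple imputation.

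The schedule in Table 1 already collects every value needed at baseline, 3, 6 and 12 months, and SPSS fits both models. The cost is wording and some analysis time, with no extra visits or participants. A two-sample test of change would also cure the basic defect, but it gives up the precision gained from baseline adjustment.

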### 2.12. Provisions for post-trial care

The participants will be regularly followed-up in the outpatient clinic of the Department of Rehabilitation Medicine. Adverse events or worsening of symptoms will be evaluated and monitored by physicians and annual CPET examinations.

### 2.13. Ethical approval and consent to participate

Approval from the IRB was obtained prospectively before conducting the research, and the board agreed to confirm the implementation and process of the research. Ethical approval was obtained from the Research Ethics Committees of Chungnam National University Hospital (CNUH 2021-01-025) and Chonnam National University Hospital (CHUH-2021-100) through peer reviews.

#### 2.13.1. Consent process of participants.

The objectives and methods of this clinical study will be explained to the participants through an explanatory text, and only subjects who know the objectives of the study and have a written consent form will participate in the study. The records identifying the subjects will be kept confidential, and the identity of the subjects will remain confidential if the results of the clinical study are published. Consent will be obtained by specifying and explaining that the subjects may discontinue participation at any time during the research period. The principal investigator and the patient physician will fully explain the study to the participants and obtain written consent. Only the participants will be able to provide consent, and they will be given sufficient time to think and make their own decisions. The researcher or physician will not encourage participants to provide consent, and if necessary, the participants will be given time to go home, think over, and sign the consent form.

#### 2.13.2. Protocol amendments.

Interim analysis and reports will be provided once a year to the IRB, and if modifications are required for the study protocol, permission will be granted by the IRB and it will be reported to the trial registry. In the event of changes in the study protocol or changes based on DMC reports and adverse reaction analysis, such changes will be reported, and corresponding permission will be received from the IRB or the Korea Disease Control and Prevention Agency.

### 2.14. Privacy measures for participants

#### 2.14.1. Storage method and storage period.

The medical records of the patients (registration number) and pathology numbers will be kept in a separate file under the responsibility of the researcher-in-chief. Each patient will receive a unique code number so that the identification of personal information is prohibited through the research data. The data will be entered into a spreadsheet and stored in a locked cabinet. According to Article 15 of the Enforcement Rules of the Bioethics and Safety Act in Korea, records related to research will be preserved for 3 years from the date of research completion.

#### 2.14.2. Destruction method.

Documents containing personal information that pass the 3-year retention period will be destroyed in accordance with the relevant laws and regulations. Electronic files will be permanently deleted. Paper records such as printed materials and signatures will be shredded or incinerated. Documents will be destroyed in accordance with Article 16 of the Enforcement Decree of Personal Information Protection.

## 3. Discussion

CR is an essential treatment process with proven safety and effectiveness in improving exercise capacity, quality of life, and prognosis of patients with cardiovascular disease, and is currently being implemented in 111 countries worldwide. Scotland (SIGN: The Scottish Intercollegiate Guidelines Network),^[15]^ the UK (NICE: National Institute for Health and Clinical Excellence),^[16]^ the U.S. (AHA: American Heart Association),^[17]^ Europe (ESC: European Society of Cardiology),^[18]^ Canada (CACR: Canadian Association of CR),^[19]^ and Japan (JCS: Japanese Circulation Society)^[20]^ have already published clinical practice guidelines for CR with a high level of evidence and strong recommendations. In Korea, clinical practice guidelines for CR^[21]^ were developed with the support of the Health and Medical Research and Development Project of the Korea Health Industry Development Institute and are distributed to related academic societies and cardiovascular hospitals.

However, because of various factors that impede participation in CR, the actual participation rate among patients in need of CR remains low, at approximately 30% to 40%, even in medically advanced countries.^[6]^ Each country is striving to increase its participation rate in cardiac rehabilitation. Conversely, Korea reports even lower levels because of reasons such as lack of awareness regarding the concept and importance of CR by physicians and patients; lack of cardiac rehabilitation specialists and facilities; and logistic barriers, such as distance, time, and cost. Currently, cardiac rehabilitation programs are implemented in approximately 40 university hospitals and cardiovascular hospitals nationwide, including 11 regional cardiocerebrovascular disease centers. Korea has a considerably lower level of 5%, which is significantly lower than that of the aforementioned medically advanced countries. Moreover, despite the implementation of cardiac rehabilitation health insurance benefits initiated in February 2017, the statistics show that only 26 hospitals filed claims for CR health insurance in 2018, suggesting that CR has not yet been properly implemented in Korea.^[10]^ Although clinical practice guidelines for CR have already been developed domestically and internationally, the implementation practice rate and outcomes, such as dissemination and distribution of the guidelines in hospital clinical sites, are insufficient.

This study is for patients who were referred for CR after hospitalization in the cardiology department for acute MI. This study aims to compare the effectiveness of offering CR incentives to CR-eligible patients with traditional CR. Therefore, additional efforts to increase CR participation in Korea are urgently required. This study has several strengths. This is the first Asian study to assess the effect of financial incentives on increasing CR participation and completion. The results may help establish more efficient guidelines for the national CR program and improve CR participation. Such effects may help reduce the recurrence of MI, improve patients quality of life, and increase the rate of return to the social workplace.

This study has limitations. It does not consider economic status in the selection process of the subjects. The effect of financial incentives may be emphasized in a patient population with low economic status; however, in Korean healthcare, such a population already receives financial support from the National Healthcare Insurance policy. Another limitation is that this study will be centered on tertiary hospitals; thus, it is expected that it may be difficult to apply the research conclusions to local regional clinics. However, the results of this study will be utilized efficiently in establishing effective CR programs in South Korea, because the national CR guidelines are based on tertiary hospital settings.

This study is supported by a grant from the Department of Cardiovascular Disease, Korea National Institute of Health, Korea Disease Control and Prevention Agency (Grant No. 2020ER630500). The data and results will be reported to the Korean National Institute of Health and submitted for publication in peer-reviewed journals and international conferences.

## 4. Conclusion

This study aims to compare the effect of providing CR financial incentives to post-MI patients referred for and eligible for outpatient CR and to confirm the effect of increasing the participation rate and completion rate of CR. Future studies investigating specific barriers to CR in Asian populations, especially South Korea, may help alleviate the low CR participation rate and emphasize the results of this study. The data and results can be used to improve and design new health program guidelines for cardiovascular rehabilitation.
